### Randomization and allocations

2.6

With reference to related reports, we are intended to use the method of random number table (Brocklehurst & Hoare, 2017) to randomly divide the included candidates into open endotracheal suctioning group and closed endotracheal suctioning group. We have aimed to blinding staff and patient intervention selection at the point of randomization, but once the intervention occurs then nurses can no longer be blinded. And the nurse will conduct the open and closed endotracheal suction accordingly.

### Blindness

2.7

We are going to only set blindness on patients with similar suction equipment, limited by the number of nursing staff, and we will not set blindness on the nurses during intervention and outcome assessments.

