### Study design

2.1

This study is designed as a single‐blinding, single‐centre randomized controlled trial (RCT), and the flow chart of study design is presented in Figure 1. We will perform blinding to the included patients, but we do not apply the blinding to the interventionists and the outcome observers.

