### The suction intervention

2.8

In this study, the open and closed endotracheal suction will be performed accordingly in two groups. Before suctioning, both groups of children will undergo the same dose of pure oxygen. And chest percussions will be performed before suction. All the patients will be put in supine position during suction since the change of position can affect the ICP, and the stableness of ICP is vital to the management of TBI patients. The open suctioning group will use a single ordinary suction tube (Pacifi, China) for sputum suction after detachment from the ventilator, while for the closed endotracheal suction group, a specific tube (Geri, China) for sputum suction will be used. That is, the closed sputum suction tube was inserted from one end of the Y‐connector of tracheal intubation for intratracheal suction. Suction will be performed whenever patient needs, and the suction pressure used will be controlled under 80–100 mmHg. The duration of every suction is intended to be less than 15 s, and the suction can be proceeded until obtaining the sputum within 15 s.

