## RESULTS

3

Our study is planned to commence on 1 September 2020 and is expected to run until 31 August 2022, with a total duration of 24 months. We will use the intention‐to‐treat analysis to retain the randomized information as much as possible, and we will compare and adjust the characteristics to minimize the homogeneity of participants. We have conducted a pilot study with four patients to check the feasibility of the study, and it is feasible in our department. And based on the results of pilot study, we expected that the closed suctions may have more advantages in stabilizing the ICP level, and it may have the equal effects in the suctioned sputum volume and preventing the VAP. The results are expected to be shared in August 2022.

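### Similar equipment cannot conceal the arm, and unblinded outcome assessment leaves the readings around each suction, the sputum estimate and the VAP diagnosis open to observer bias

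*Protocol article*

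**What the plan says.** The abstract calls the trial single-blind, and section 2.1 (Study design) explains what is meant: "We will perform blinding to the included patients, but we do not apply the blinding to the interventionists and the outcome observers". Section 2.7 (Blindness) names the means of blinding the children, "We are going to only set blindness on patients with similar suction equipment", and adds, citing nurse numbers, "we will not set blindness on the nurses during intervention and outcome assessments". Section 2.6 (Randomization and allocations) accepts that "once the intervention occurs then nurses can no longer be blinded".

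Section 2.8 (The suction intervention) describes the two techniques. The open arm "will use a single ordinary suction tube (Pacifi, China) for sputum suction after detachment from the ventilator". In the closed arm "a specific tube (Geri, China) for sputum suction will be used", introduced through one end of the Y-connector.

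Section 2.9 (Outcome assessment) lists ICP, SpO2 and heart rate at four time points around suction, estimated sputum volume, VAP, days of ventilation and days in ICU. None is named as primary. Section 3 (Results) records the team's expectation from its pilot: "we expected that the closed suctions may have more advantages in stabilizing the ICP level".

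**The concern.** There are two problems. First, the reason given for patient blinding does not fit the interventions as described. If tube, connection and ventilator disconnection all differ, the equipment does not disguise the arm.

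Second, blinding matters where someone who knows the arm can influence what is recorded. Here that is the staff who suction and the observers who assess outcomes, and they are the people left unblinded. ICP fluctuates in these children, as the Background says. A reading taken before suction or at its end depends on exactly when it is taken, and the article fixes neither moment. A small systematic difference between arms in how values are picked or written down would look like an effect of the suction method. It would also not shrink as more children are recruited.

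**Working it through.** **Step 1. Does the stated means of blinding fit the interventions?**

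| Feature | Open arm (2.8) | Closed arm (2.8) |
|---|---|---|
| Tube | ordinary single tube, one make | dedicated tube, another make |
| Connection | used once the child is off the ventilator | through the Y-connector |
| Ventilator | detached | not detached |

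All three differ. The equipment similarity claimed in section 2.7 is not what section 2.8 describes.

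**Step 2. What would patient blinding protect?** Section 2.9 lists monitored values (ICP, SpO2, heart rate), a staff estimate (sputum volume), a clinical diagnosis (VAP) and two durations. None is reported by the child, so whether the child knows the arm has no direct route into any of them.

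**Step 3. Where could an unblinded observer make a difference?**
- ICP, SpO2 and heart rate: the 5 and 10 min readings have a nominal time. The pre-suction and end-of-suction readings have no clock definition or averaging window. Bias could enter through the moment chosen or through transcription.
- Sputum volume is an estimate, and VAP needs a diagnostic judgement even under guidelines. Both leave more room for opinion than a monitor value.
- Selection of episodes: the limitations paragraph in section 4 (Discussion) admits that some suction episodes may be missed or recorded late.

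**Step 4. How sensitive is the comparison to a small shift?** The plan has no figure of its own to reproduce on this point, so this is an illustration.

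Inputs:
- n = 78 per arm, from section 2.5, before the allowance for attrition.
- Two-sided α = 0.05 and an independent t test, from sections 2.5 and 2.10.
- Between-child SD of ICP, 5 to 8 mmHg: assumed.
- Systematic difference in recorded ICP between arms, b = 0.5 or 1 mmHg: assumed.
- No true treatment difference, and one ICP value per child: simplifications.

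Formulas: SE = SD × √(2/n). Noncentrality δ = b / SE. The false-positive rate is P(|T| > 1.976), where T is noncentral t with 2 × 78 − 2 = 154 degrees of freedom and noncentrality δ.

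Example with SD 5 and b = 1: SE = 5 × √(2/78) = 0.801, δ = 1/0.801 = 1.25, rejection probability 0.237.

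| SD (mmHg) | SE | b = 0 | b = 0.5 | b = 1 |
|---|---|---|---|---|
| 5 | 0.801 | 0.05 | 0.095 | 0.237 |
| 6 | 0.961 | 0.05 | 0.081 | 0.179 |
| 8 | 1.281 | 0.05 | 0.067 | 0.121 |

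With the full 86 per arm, b = 1 gives about 0.26 (SD 5) to 0.13 (SD 8). The error rate rises slightly, because a larger sample detects a fixed bias more readily.

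**The case against.** The strongest reply is that nothing is hidden. Section 2.1 defines single-blind as patient-only, which is a conventional use of the term, and says outright that "we do not apply the blinding to the interventionists and the outcome observers"; section 2.7 repeats it with a reason. That stands. A reader might infer that the trial is not single-blind at all and is mislabelled. The documents do not support this. Different equipment shows that the stated explanation fails, not that the children know their arm. The sedation or awareness of severely brain-injured, ventilated children is not described. Relabelling the trial as open-label would by itself change no result.

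A reader might also infer that the suctioning nurse takes the ICP, SpO2 and heart-rate values and chooses the moment. No section says so, and section 4 mentions a research team that collects data. What the text does establish is that outcome observers are unblinded, and the argument needs only that. Nor is ICP formally the main outcome: it is in the title and first in the list, but none is named primary.

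It can further be said that three of the outcomes are numerical, that two of the four time points have a nominal time, and that capture procedures may be set out in a fuller protocol. The first two points reduce the scope for bias without removing it. On the third, the missing detail is not held against the article. The point rests on what it does state: unblinded assessment, and a reason for blinding that its own description contradicts.

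Lastly, both the shift and the SDs are assumed, and a pilot-based expectation in favour of one arm is common and openly disclosed. This is correct. The calculation shows how sensitive the test is, not that a bias exists.

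**Conclusion.** The point holds in a limited form. Section 2.7 contradicts section 2.8 on how patients are blinded, and patient blinding guards none of the listed outcomes. Outcome assessment is unblinded by the article's own account, and two of the four reading times are loosely defined. ICP, SpO2 and heart rate are exposed to observer bias; estimated sputum volume and VAP diagnosis are more exposed.

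The size of any bias cannot be derived from the documents. If the assumed SDs are about right, a consistent half-millimetre shift would be a modest problem, and a full millimetre would inflate the type I error to between roughly two and five times its nominal level. This is a cheap improvement to make, and not evidence that the result will be biased.

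**What to change.** 1. Reconcile section 2.7 with section 2.8 and drop equipment similarity as the basis of blinding. Keep the plain statement that staff and outcome observers know the arm.
2. Take ICP, SpO2 and heart rate from the bedside monitor's time-stamped record at defined moments. One example is a short mean just before suction starts, then values at catheter withdrawal and at 5 and 10 min after it. This assumes that the stored records can be retrieved, which the documents do not say.
3. Keep the arms coded A and B until the main analysis is final.

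The monitor record does not cover sputum volume or VAP. For VAP, having the diagnosis confirmed by someone not told the arm would be a sensible extra where staffing allows.

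The three changes alter neither the suction procedures nor the sample size, and they need no additional assessor, so the staffing limit in section 2.7 does not stand in the way. The cost is rewording plus the time to extract the stored values.

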### The suction intervention

2.8

In this study, the open and closed endotracheal suction will be performed accordingly in two groups. Before suctioning, both groups of children will undergo the same dose of pure oxygen. And chest percussions will be performed before suction. All the patients will be put in supine position during suction since the change of position can affect the ICP, and the stableness of ICP is vital to the management of TBI patients. The open suctioning group will use a single ordinary suction tube (Pacifi, China) for sputum suction after detachment from the ventilator, while for the closed endotracheal suction group, a specific tube (Geri, China) for sputum suction will be used. That is, the closed sputum suction tube was inserted from one end of the Y‐connector of tracheal intubation for intratracheal suction. Suction will be performed whenever patient needs, and the suction pressure used will be controlled under 80–100 mmHg. The duration of every suction is intended to be less than 15 s, and the suction can be proceeded until obtaining the sputum within 15 s.

### Outcome assessment

2.9

The outcomes collected and analysed in this present study are as follows: (a) the ICP (mmHg) level before suctioning, at the end of suctioning, and at 5 and 10 min after suctioning; (b) the pulse oxygen saturation (SpO_2_,%) and heart rate (times/min) before suctioning, at the end of suctioning, and at 5 and 10 min after suctioning; (c) the estimated sputum volume (ml) for each suction; (d) the incidence of ventilator‐associated pneumonia(VAP): the diagnosis and treatment of VAP will be in comply with related guidelines (Ardehali et al., 2020; Liapikou et al., 2019; Shi et al., 2019); (e) the duration of mechanical ventilation (days); and (6) the length of ICU stay (days).

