## BACKGROUND

1

Brain injury is a common serious problem with extremely high mortality and disability rates in clinical settings, which is very common in car or fall accidents (Capizzi et al., 2020). It has been reported that the incidence of traumatic brain injury ranks the second among the trauma of various body organs, but the mortality of traumatic brain injury ranks the first (Dewan et al., 2016). Previous studies (Cheng et al., 2017; Taylor et al., 2017) have reported that the mortality of patients with moderate‐to‐severe brain injury in the paediatric intensive care unit (ICU) can be up to 41.9%. The brain injury not only poses a serious threat to the life and health of patients, but also places a heavy economic and spiritual burden on their families and society (Steinbuchel et al., 2020; Uski et al., 2018). Children with brain injury are often accompanied by fluctuations in intracranial pressure (ICP) (Bennett et al., 2017). Those patients with severe brain injuries are prone to complications such as cerebral hernia, epilepsy and even death with regard to the disturbed intracranial pressure (Delaplain et al., 2020; Svedung Wettervik et al., 2020). Therefore, for children with severe brain injury, maintaining the stability of ICP is of great importance for the prognosis of patients.

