### Sample size calculation

2.5

We calculate the sample size with the following formula for the rate comparison of two groups (Sakpal, 2010):$$n=\frac{\lambda }{2{\left(\arcsin\sqrt{P_{\max}}‐\arcsin\sqrt{P_{\min}}\right)}^{2}}$$We assume α = 0.05, β = 0.2 and ν = 3–1 = 2, then λ = 8.84, and we set *P*
_max_ and *P*
_min_ as the maximum and minimum fluctuation rates of during sputum suction in our pre‐trials (54.6% and 20.9%, respectively), then we come to the result of *n* ≈ 78. Furthermore, considering that the attrition rate of about 10% of the study participants, the number of patients included in each group should be at least 86. Therefore, a total of 172 patients are intended to be included.

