### Statistical analysis

2.10

SPSS 23.0 software will be used for data analysis in the present study. The enumeration data will be expressed with mean ± standard deviation (*SD*), and the categorical variable data will be expressed with percentages (%). Test for normality will determine whether to use parametric test (independent *t* test/paired *t* test) or (Mann–Whitney test/ Wilcoxon's test). In this present study, *p* < .05 will be considered statistically significant.

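### Raw ventilation days and ICU days are compared with no account of death, so if suction method truly affects the number or timing of deaths, the arm with more early deaths looks better

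*Protocol article*

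**What the plan says.** Section 2.9 (Outcome assessment) ends its outcome list with "the duration of mechanical ventilation (days") and "the length of ICU stay (days"). Both are plain counts of days. The list contains no mortality outcome, and nothing in the article says how a child who dies on the ventilator or in the ICU is counted.

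Section 2.10 (Statistical analysis) gives the tests for quantitative data: "Test for normality will determine whether to use parametric test" or a rank test. It names no time-to-event, competing-risk or composite method.

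Section 3 (Results) specifies an intention-to-treat "analysis to retain the randomized information as much as possible", so children who die stay in the comparison. It also mentions adjusting for characteristics, which does not deal with death.

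Section 1 (Background) puts mortality in moderate or "severe brain injury in the paediatric intensive care unit (ICU) can be up to 41.9"%.

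**The concern.** A short time on the ventilator or in the ICU reads as a good result. A child can reach it by recovering or by dying early, and raw days do not separate the two. If the arms differ in early deaths, the arm with more of them gains short durations for the wrong reason. Because mortality is not a listed outcome, a reader of the results could not see that this had happened.

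The trial's own reasoning makes a difference in deaths conceivable. The Background links disturbed intracranial pressure to death, and the Results section expects closed suction to stabilise that pressure better. If that chain held, the arm protecting more children could look worse on both durations.

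**Working it through.** The plan gives no figure for either duration, so there is none to reproduce. The check asks how far raw days mislead when only mortality differs.

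**Inputs from the article**
- 86 children per group, 172 in total (section 2.5).
- Significance at p < .05 (section 2.10).
- Cited mortality ceiling 41.9% (section 1). At that ceiling, 0.419 × 172 ≈ 72 children would die.

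**Assumed, because the article gives none of these**
- Ventilation need lognormal with median 9 days and log-SD 0.6, identical in both arms.
- Time to death exponential with mean 3 or 5 days.
- Mortality between 5% and 41.9%.
- Observed days for a child who dies = the smaller of time to death and ventilation need.

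**Size of the shift.** Difference in mean days ≈ mortality difference × (survivor mean − decedent mean).
- Survivor mean: 9 × exp(0.6²/2) = 9 × exp(0.18) ≈ 10.8 days.
- Decedent mean: t × (1 − E[exp(−L/t)]), where t is the mean time to death and L the ventilation need. This is about 2.7 days for t = 3 and 4.0 days for t = 5.
- Gap: 10.8 − 2.7 = 8.1, or 10.8 − 4.0 = 6.8 days.
- A 10-point mortality difference gives 0.10 × 8.1 = 0.81 or 0.10 × 6.8 = 0.68 days, in favour of the arm with more deaths.

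**Simulation.** 4,000 trials per setting, 86 per arm, Mann–Whitney test. The ranges run over the two mean times to death.

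| Mortality, arm A vs arm B | Raw days: B shorter by | Raw days: p < .05 favouring B | Ventilator-free days to day 28, death = 0: B lower by |
|---|---|---|---|
| 5% vs 10% | 0.34–0.38 | 6–7% | about 0.9 |
| 20% vs 30% | 0.65–0.78 | 12–15% | 1.7–1.8 |
| 20% vs 41.9% | 1.5–1.8 | 43–57% | 3.8–3.9 |

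The nominal rate in the third column is 2.5%. The simulated shifts agree with the formula. In each row the lower raw-day figures belong to the later deaths. On ventilator-free days the sign reverses, and the arm with more deaths looks worse.

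**Equal mortality.** With 20% or 41.9% in both arms, the raw-day test rejects in about 5% of trials, split evenly between directions.

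The simulation covers ventilation days and the rank test. ICU days are shortened by death in the same way but were not simulated separately.

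**The case against.** The strongest reply is that the article is silent on deaths rather than wrong about them. A journal article condenses, and an analysis plan that is not shown could say how deaths are counted. This stands in part: no sentence says that a death on day 2 scores as a two-day success, and a reader should not infer such a rule. But the article does fix the endpoint as raw days, names the tests, keeps every randomised child and leaves death off the outcome list. Followed as written, that lets early deaths enter as short durations.

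Three stronger readings are tempting and are not supported:
- **That chance imbalances in deaths inflate the error rate.** They do not. Such imbalances are already present when true mortality is equal, and rejection stays near 5%. A chance imbalance can shift one trial's estimate, but excess false positives need a real effect on deaths.
- **That 41.9% is the trial's expected mortality.** It is an upper value from cited studies of moderate-to-severe injury. The trial makes no mortality assumption and excludes several groups of sicker children.
- **That error rates near one half should be expected.** These need a real mortality difference of about 20 points. The article gives no reason to expect one, and its Discussion cites an adult meta-analysis in which closed suction did not reduce mortality, while noting the limited quality of its trials. In a similar model (78 per arm, log-SD 0.5), a 3-point difference raises two-sided rejection only to about 6%. There, moving the mean time to death from 3 to 7 days lowers rejection from 46% to 24% for a 20-point difference.

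It is also fair that these are not the intracranial-pressure outcome of the title, and that the Results section states no expectation for either duration.

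**Conclusion.** The point holds in conditional form. The chosen endpoints and tests favour the arm with more early deaths if suction method truly affects the number or timing of deaths, and the planned outcomes would not reveal it. If it does not, the comparison keeps its level.

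The direction follows from the article alone. The size does not: it depends on mortality by arm, timing of death and ventilation times, none of which is given. Under the stated assumptions the false-favouring rate runs from slightly above nominal (6–7% against 2.5%) for a 5-point difference to 43–57% for a difference of about 22 points. This should be corrected because the remedy is cheap, but it does not touch the trial's main question on intracranial pressure.

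**What to change.** For these two outcomes:
1. Use the Mann–Whitney test outright, with deaths ranked worst. Alternatively, define ventilator-free and ICU-free days over a stated fixed horizon with deaths scored 0. The article sets no horizon; day 28 above is only an illustration.
2. Report ICU mortality by arm beside them.
3. Give raw durations as description only, separately for survivors and non-survivors.

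The cost is a few sentences of analysis text plus each child's vital status and date of death, which an ICU would ordinarily record although the article does not list them. With a fixed horizon, status must also be known to its end. The drawback is that the new endpoint mixes mortality with duration and is less intuitive than raw days, which is why mortality should stand beside it.

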### Statistical analysis

2.10

SPSS 23.0 software will be used for data analysis in the present study. The enumeration data will be expressed with mean ± standard deviation (*SD*), and the categorical variable data will be expressed with percentages (%). Test for normality will determine whether to use parametric test (independent *t* test/paired *t* test) or (Mann–Whitney test/ Wilcoxon's test). In this present study, *p* < .05 will be considered statistically significant.

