ICP monitoring plays an important role in the treatment and prognosis of patients with brain injury. Several previous studies (Argent, 2019; Chen et al., 2019; Miles et al., 2020) have shown that there is a significant correlation between the changes in ICP and cerebral blood flow perfusion with various treatment and nursing procedures. The nursing operation of suction can lead to transient increase in ICP, but its long‐term effects remain unclear. Giancarlo et al (Galbiati & Paola, 2015) have systematically analysed 14 related studies and have pointed out that although the risk of ICP increasing above 20mm Hg during open suction is higher, it is still unclear which suction approach is more conducive to the maintenance of ICP and brain blood perfusion balance. Therefore, further research is needed to determine the best suction technique for nursing practice.

Several limitations must be considered in this present study. Firstly, even though we have organized a research team to collect the data, we cannot ensure all the normal nursing staff will follow the procedures as we designated, we cannot ensure data are collected on every suction episode, especially for those patient requires emergency suctioning, and the data may not be collected timely. We will conduct several trainings on the details of our procedure to ensure the accuracy of collected data. Secondly, sample size is not large in this present study, and there may be some differences in the suction pressure among different populations, and future studies with larger sample size and multi‐centre are needed.

To the best of our knowledge, there are very few studies focused on the role of open and closed endotracheal suctions and potential effects on the ICP in the children population. In this present study, we have aimed to assess the potential effects of open and closed endotracheal suction on ICP in the population of children, to provide credible evidence to the nursing care of airway. The results of this study are expected to provide basis for the suction practice of airway management in children.

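### Section 2.10 names only tests for independent observations and does not say how a child's repeated suction episodes enter them

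*Protocol article*

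**What the plan says.** Section 2.6 of the protocol article randomises children to open or closed suctioning. Section 2.5 counts the sample size in patients: 86 per group, 172 in total.

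The number of suctions per child is not fixed. Section 2.8 says "Suction will be performed whenever patient needs".

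Section 2.9 lists the outcomes to be collected and analysed. One of them is "the estimated sputum volume (ml) for each suction". Another is "the ICP (mmHg) level before suctioning, at the end of suctioning, and at 5 and 10 min after suctioning", and SpO2 and heart rate follow the same four times. The limitations paragraph of the Discussion adds that "we cannot ensure data are collected on every suction episode, especially for those patient requires emergency suctioning", which implies that collection on every episode is what the team is aiming for.

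Section 2.10 then fixes the tests: "Test for normality will determine whether to use parametric test (independent *t* test/paired *t* test" on the parametric side, and "Mann–Whitney test/ Wilcoxon's test" otherwise. It does not state the unit of analysis. The Results section promises intention-to-treat analysis and adjustment for characteristics, but names no model and does not mention repeated episodes.

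**The concern.** The data described have up to three levels: time points within an episode, and episodes within a child. The independent t test and the Mann–Whitney test assume that every observation is independent of the others. The paired t test and Wilcoxon's test assume that the pairs are. Several episodes from one child meet neither condition.

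Two things go wrong if episodes are entered as separate observations.

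- **Precision is overstated.** The effective number of observations is smaller than the number of episodes, so standard errors are too small and the type I error exceeds 5%. This would affect sputum volume and, if they are collected on every episode, ICP (the outcome in the trial's title), SpO2 and heart rate.
- **The weighting no longer follows randomisation.** A child with many recorded episodes counts more than a child with few. That count arises after randomisation. It depends on nurses who know the allocation (sections 2.1 and 2.7) and on recording that the Discussion expects to be least complete for emergency suctions.

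**Working it through.** **Plan's own figure.** There is none to reproduce on this point. The article gives no number of episodes per child and no within-child correlation.

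**Inputs from the article.** The child is randomised (2.6). Suction is on demand (2.8). Sputum volume is per suction, and ICP, SpO2 and heart rate are measured at four times around suctioning (2.9). The tests are t and rank tests, judged at p < .05 (2.10).

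**Inputs assumed.** Episodes per child, m = 2 to 50, equal across children. Intraclass correlation of the analysed quantity within a child, ICC = 0.05 to 0.5.

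**Formulas.**
- Design effect: DE = 1 + (m − 1) × ICC
- Naive standard error divided by true standard error: 1/√DE
- True two-sided error of a nominal 5% test: 2 × [1 − Φ(1.96/√DE)]

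**Worked example, m = 10, ICC = 0.3.** DE = 1 + 9 × 0.3 = 3.7. The standard error ratio is 1/√3.7 = 0.52. The true error is 2 × [1 − Φ(1.96 × 0.52)] = 2 × [1 − Φ(1.02)] = 0.308.

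| m | ICC | DE | SE ratio | True error |
|---|---|---|---|---|
| 2 | 0.05 | 1.05 | 0.98 | 5.6% |
| 5 | 0.1 | 1.4 | 0.85 | 9.8% |
| 5 | 0.3 | 2.2 | 0.67 | 18.6% |
| 10 | 0.3 | 3.7 | 0.52 | 30.8% |
| 20 | 0.3 | 6.7 | 0.39 | 44.9% |
| 50 | 0.5 | 25.5 | 0.20 | 69.8% |

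**Check by simulation.** Normal data with no true difference, 78 children per arm, 2,000 runs per setting:

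| m | ICC | Episode-level t | Episode-level Mann–Whitney | t test on child means |
|---|---|---|---|---|
| 5 | 0.3 | 16.8% | 16.5% | 4.7% |
| 10 | 0.1 | 14.1% | 14.3% | 5.3% |
| 10 | 0.3 | 32.1% | 31.0% | 5.3% |
| 20 | 0.3 | 44.1% | 43.3% | 4.9% |

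The simulation agrees with the formula. Moving from the t test to the rank test gives no protection. Reducing each child to one value restores the 5% level.

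Both calculations use the same m for every child, so they show only the loss of precision. They do not measure the weighting problem.

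**The case against.** The strongest reply is that section 2.10 names tests without a unit of analysis, and that these tests are valid on one value per child; the last column of the simulation shows this. Wherever the article does mention a unit, it is the child: randomisation, sample size, attrition and intention-to-treat all refer to patients. A condensed article may also leave the reduction step to a fuller plan.

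Much of this stands, and it rules out several stronger readings that a reader might infer.

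- *That the plan will pool episodes.* The article does not say so. The inflated error is conditional on pooling.
- *That ICP, SpO2 and heart rate are stated to be recorded on every suction.* Only sputum volume is. For the others, section 2.9 gives four times without a number of episodes, and every-episode collection is inferred from "we cannot ensure data are collected on every suction episode".
- *That the named tests cannot handle four time points.* With one episode per child, a paired test of before against after, or a between-arm test at each time, is valid. What then remains is efficiency and multiplicity, which is a different matter.
- *That the error will be near 45%.* That figure needs m = 20 and ICC 0.3, neither of which is in the article. At m = 2 and ICC 0.05 the inflation is almost nothing.
- *That the planning rates of 54.6% and 20.9% show the team already counts episodes.* These could not be patient rates from the four-patient pilot, where only multiples of 25% are possible. But the article does not say that its pre-trials are that pilot.

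The objection does not remove the point. This is more than silence about a detail: the article itself fixes the tests, describes one analysed outcome per suction, and supplies nothing to connect the two. As it stands, the unit of analysis could be chosen after the data are seen.

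**Conclusion.** The concern holds in conditional form. The tests named in section 2.10 do not fit the repeated-episode data described in sections 2.8 and 2.9 unless each child is first reduced to one value, and the article includes no such step.

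If episodes are entered as separate observations, the direction of the error is certain for any positive within-child correlation and more than one episode per child. Its size cannot be fixed from the article. Over the assumed grid, the true error of a nominal 5% test runs from 5.6% to about 70%. Unequal weighting by recorded episodes comes on top of that, and a larger trial would not remove it.

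The point applies directly to sputum volume and, on the every-episode reading, to ICP, SpO2 and heart rate. VAP, duration of ventilation and length of ICU stay have one value per child and are not affected.

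**What to change.** In section 2.10, state that the child is the unit of analysis for ICP, SpO2, heart rate and sputum volume, and fix one of two routes before the data are seen.

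1. **One value per child, compared with the tests already named.** This could be the child's mean change across recorded episodes, or the first recorded suction after randomisation regardless of urgency. Restricting to non-emergency suctions should be avoided, because unblinded staff would make that classification after randomisation.
2. **All episodes in a linear mixed model.** For ICP, SpO2 and heart rate, include arm, time point, arm × time, and random effects for child and for episode within child. Sputum volume has one value per episode, so its model needs only arm and a random effect for child. SPSS 23 MIXED can fit both.

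If ICP is adjusted for baseline, use the value before the child's first suction, and do not also model that value as an outcome. Pre-suction values of later episodes arise after randomisation and may be affected by the arm.

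Report the number of recorded episodes per child by arm, and unrecorded episodes where known. Neither route by itself cures selective recording, so these counts are needed to judge it.

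The cost is a change of wording, a little more analysis work, and wider intervals than a pooled analysis would show. Counts of unrecorded episodes are not among the data listed in section 2.9, so they would need to be logged where possible.
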